### Data management

All personal information such as date of diagnosis, relevant medical and social history will remain confidential. Participants will be given a unique number which will be used on paperwork, assessment score sheets and in the names of all video files, and in all subsequent analysis documents and publications. Lists of participant names and their unique numbers (required to conduct the remote randomisation procedure) will be kept by a designated local collaborator in a locked cabinet at each NHS site. Each list will only contain the names of participants based at the relevant site.

Participants will consent to be video recorded in conversation for the purposes of outcome measurement and to provide clips for video feedback during intervention sessions. Participants’ faces will be fully visible in these video recordings as people’s expressions form a significant part of natural human communication, the focus of the intervention being piloted. Confidentiality can be guaranteed in the sharing of this footage at conferences and during teaching activities but not anonymity. Judicious selection of recordings will minimise this risk (e.g. footage where personal details are discussed will not be used, and names will be blanked out of the audio stream). Allied health professionals viewing this footage are bound by professional codes of ethics requiring them to maintain client confidentiality. Participants (and their CPs) will be asked whether they are willing to accept the possibility of being recognised, and can opt out of this use of their data whilst remaining part of the study. Only the research team members will have access to the entire video recorded data set. All transcripts of conversation data will be anonymised by the use of pseudonyms for all named people and places.

No data management committee will be established as it is felt that this short, small-scale pilot carries minimal risks. The study is compliant with General Data Protection Regulations. If information disclosed by any participant leads the first author to believe that a participant is at risk of harm or harming others, confidentiality will be broken to ensure safety.

### Data analysis

Analysis for this single blind, randomised controlled pilot study will involve both quantitative and qualitative methods. Language and quality of life assessment data will be entered into a database and analysed using the Statistical Package for the Social Sciences [33]. All data will be explored to test for assumptions of normalcy. If assumptions are not met, appropriate non-parametric tests will be used. Repeated measures ANOVA will be used in the analysis with group (no speech and language therapy treatment, BCPPA treatment) as a between subject factor and time (pre-therapy and post-therapy) as a within subject factor. This information will be used to determine a suitable sensitive outcome measure and to perform a power calculation to determine sample size for a fully powered trial. Conversation data will be analysed following a procedure developed for the BCA intervention [21] to identify change in the use of targeted strategies following intervention. This will involve counting barrier and facilitator behaviours in 5-min video samples selected from the pre- and post-intervention conversation samples. These counts will be analysed using Poisson Trend Test suitable for observations occurring in Poisson distribution. All pre-therapy conversations will be weighted the same as one another, as will all the post therapy conversations. Outcomes for different participants will be investigated using a Test for Homogeneity, where this is significant, and the effect for different dyads will be calculated using the Holm-Bonferroni procedure.

Descriptive statistics will be used to report recruitment, attendance, attrition, and reasons for dropout. A CONSORT (Consolidated Standards of Reporting Trials) and SPIRIT (Standard Protocol Items: Recommendations for Interventional Trials) [27] flow chart will be used to present overall recruitment to and progression through the study (Fig. 1). Recruitment and retention rates will be used to support sample size calculations to inform a future full trial and plan the required number of sites to meet this target. Adverse events will also be recorded, and participant feedback forms examined to inform future recruitment procedures. Stroke-related aphasia trials in the UK NHS have reported recruitment rates of between 38 and 44% from potential participants at the research sites [34–36].

Analysis of fidelity and adherence data will inform future training needs. Although fidelity data is sparse for speech and language intervention trials, processes such as those deployed in our study have been shown to achieve an average of 80–100% fidelity [37–39]. Thus, we have selected 80% as the minimum target for fidelity. Acceptability of the intervention will be considered, based on analysis of the participant feedback forms and adherence data to inform further refinements of the intervention prior to a future full trial. Analysis of participant feedback and adherence data will use descriptive statistics. For open-ended questions or ‘other’ response categories, qualitative analysis will be used, specifically identifying themes and sub-themes using thematic analysis [40].

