### Randomisation

Randomisation will be conducted by the final author using a random number generator and stratified by site using blocks of four to balance across BCPPA treatment and no speech and language therapy treatment groups within each site. Block sizes will not be disclosed to local collaborators. Local collaborators will be informed of participant group allocation via email after pre-assessment has been completed.

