### Sample size justification

As there are no data available to estimate a sample size, the recruitment of participants has been dealt with pragmatically. Based on discussion with clinicians at the primary research site, it is estimated that it will be possible to recruit 42 participants over an 18-month period at seven sites. This pilot will provide information on recruitment and retention and facilitate a sample size calculation for a future full trial. Recruitment will be reviewed at 2-month intervals during the study, and the recruitment strategy will be amended as necessary to achieve the target number.

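### Pre/post scores are analysed by two-time-point repeated measures ANOVA, which is valid but less precise than ANCOVA on baseline, and the open switch to non-parametric tests puts candidate outcomes on different scales

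*Protocol article*

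**What the plan says.** The Data analysis section names the model for the language and quality of life scores: "Repeated measures ANOVA will be used in the analysis with group" as the between-subject factor and "time (pre-therapy and post-therapy) as a within subject factor". It names no baseline covariate and no site term. Distributional assumptions are to be checked, and "If assumptions are not met, appropriate non-parametric tests will be used"; the tests are not named.

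The same section gives the purpose of these analyses: "This information will be used to determine a suitable sensitive outcome measure and to perform a power calculation to determine sample size" for the later trial. The Aim section lists the choice of primary outcome and the sample size calculation among the things the pilot must establish, and Criteria for success makes both a condition for proceeding.

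Two statements under Randomisation bear on the choice of model. Allocation is "stratified by site using blocks of four to balance across BCPPA treatment and no speech and language therapy treatment groups within each site". And "Local collaborators will be informed of participant group allocation via email after pre-assessment has been completed", so the baseline score cannot have been influenced by knowledge of the arm.

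**The concern.** With one score before and one after, a group-by-time ANOVA uses the baseline only by subtraction, with its coefficient fixed at 1. ANCOVA estimates that coefficient and is normally more precise, and the baseline needed for it is already collected. A pilot of this size has little precision to give away, and its estimates are meant to rank several candidate measures and supply inputs for the main trial.

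The fallback adds a separate difficulty. If measures that pass a normality check are judged by ANOVA and those that fail by some other test, the comparison of sensitivity is not made on one scale. Which measures fall on which side would depend on a check made in about 42 people.

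**Working it through.** **The plan's own figure.** There is no power calculation to reproduce. The Sample size justification section sets the number pragmatically: "it is estimated that it will be possible to recruit 42 participants over an 18-month period at seven sites". That is 42/7 = 6 per site on average and, at 1:1, 21 per arm. No SD, correlation, effect size, alpha or power is given.

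**Step 1: what the planned test is.** With two time points, the group-by-time F test is the square of the two-sample t test on (post − pre).

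**Step 2: variances.** Let s² be the common pre and post variance, rho the pre/post correlation and n the number per arm. The variance of the estimated arm difference is 2/n times:
- change score: 2(1 − rho)s²
- ANCOVA: (1 − rho²)s²

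The ratio is (1 − rho²)/[2(1 − rho)] = (1 + rho)/2. Equal pre and post SDs are assumed.

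**Step 3: numbers.** Rho is assumed throughout. The minimum detectable difference (MDD, in SD units) comes from the noncentral t distribution with 21 per arm, assumed two-sided alpha 0.05 and 80% power. Degrees of freedom are 40 (change), 39 (ANCOVA) and 33 (ANCOVA plus six site terms). The ANCOVA variances are inflated for chance covariate imbalance by 1 + 1/38 without site and 1 + 1/32 with site.

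| rho | change factor | ANCOVA factor | ratio | MDD change | MDD ANCOVA | MDD ANCOVA + site |
|---|---|---|---|---|---|---|
| 0.3 | 1.40 | 0.91 | 0.65 | 1.05 | 0.86 | 0.86 |
| 0.5 | 1.00 | 0.75 | 0.75 | 0.89 | 0.78 | 0.78 |
| 0.7 | 0.60 | 0.51 | 0.85 | 0.69 | 0.64 | 0.65 |
| 0.9 | 0.20 | 0.19 | 0.95 | 0.396 | 0.392 | 0.394 |
| 0.95 | 0.10 | 0.098 | 0.975 | 0.280 | 0.280 | 0.282 |

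Expressed as dyads, ignoring degrees of freedom: at rho 0.5 the gain equals 42/0.75 = 56 dyads analysed by change score; at rho 0.9, 42/0.95 = 44.

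**Step 4: a later trial.** For an assumed 0.5 SD effect, two-sided alpha 0.05 and 80% power, n per arm = 2(1.960 + 0.842)² × factor / 0.5², about 62.8 × factor. Change score against ANCOVA: 88 and 58 at rho 0.3; 63 and 48 at 0.5; 38 and 33 at 0.7; 13 and 12 at 0.9.

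**Step 5: simulation.** Seven sites of six, blocks of four within site, 3,000 runs per setting. Type I error was about 4 to 6% for all three analyses, so the planned test is valid with or without site. Power for a 0.8 SD effect at an assumed site ICC of 0.05:

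| rho | planned interaction | ANCOVA | ANCOVA + site |
|---|---|---|---|
| 0.3 | 56% | 74% | 73% |
| 0.5 | 72% | 83% | 82% |
| 0.7 | 90% | 94% | 93% |

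With ICC 0 to 0.05, site terms lowered power by 0 to 2 points relative to ANCOVA without site. A clear gain appeared only at rho 0.3 with ICC 0.20 (79% against 76%). At rho 0.9 and ICC 0, the standard errors of ANCOVA plus site and of the change score were both 0.140.

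**The case against.** The strongest reply is that this is a feasibility pilot with no powered hypothesis, that no criterion for success requires a significant result, and that the planned test is unbiased with correct type I error. All of that stands: the point concerns efficiency and planning inputs, not validity. The size of the gain also depends on a correlation that the article does not give. Different people take the pre and post measures, which might lower it. But most of the scored measures are questionnaires or self-ratings repeated about five weeks apart, and they could correlate highly. The documents do not settle this.

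Several stronger readings are tempting and are not supported:

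- *The baseline is wasted.* It is used, through the time factor, with its slope fixed at 1.
- *ANCOVA on baseline and site is free.* Baseline takes 1 degree of freedom and fixed site effects 6 more, of about 40.
- *Leaving out site is an error that costs precision.* The simulation shows neither distorted type I error nor a material loss at 42 dyads. Adjustment for the stratification factor is also something an article may leave to a fuller analysis plan.
- *The group main effect will be read as the treatment effect.* It would halve the effect, because pre-treatment scores are averaged in, and simulated power would be about 25 to 36%. But the article does not say this term will be used, and a group-by-time design points to the interaction.
- *The fallback has no counterpart to the interaction and yields no SD.* A Mann-Whitney test on change scores is a counterpart, and SDs can be computed whichever test is run.
- *The main trial will be mis-sized.* That requires a change-score SD to be used for a trial analysed by ANCOVA. The article states neither, and the error would be a trial larger than needed.

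**Conclusion.** The point holds as one of precision and comparability. The article itself names the less precise model, so this does not rest on what an unseen analysis plan might contain. Under equal pre and post SDs, ANCOVA on baseline has 15 to 35% lower variance than the planned test for rho from 0.7 down to 0.3. The advantage shrinks to 5% at 0.9 and is then largely offset by the degrees of freedom spent. Every rho is an assumption.

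The fallback matters for a different reason. The tests are unspecified and chosen after inspecting the data, so candidate measures could be judged on different scales when the aim is to identify the most sensitive one. Nothing here suggests that the planned interaction test would give a wrong answer. The change is worth making because the gain ranges from useful to nil and the cost is very small.

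**What to change.** For each language and quality of life measure, fit the week-6 score on arm and baseline score. Report the adjusted difference with its 95% CI, the residual SD and the pre/post correlation. The last two let the main trial be sized for either analysis, and a standardised adjusted difference puts all candidates on one scale. Keep this model for every measure. If residuals are skewed, use bootstrap confidence intervals instead of changing the test after a normality check.

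Site may be added as a random intercept or fixed factor so that the analysis matches the stratified design, without expecting it to add much precision at 42 dyads.

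The cost is a change of analysis wording only, since every variable is already collected: 1 degree of freedom for baseline, and up to 6 more of about 40 if site is fitted as fixed.

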**Methods:**

A single blind, randomised controlled pilot study will recruit 42 participants with primary progressive aphasia and their conversation partners across seven UK National Health Service Trusts. Participants will be randomised on a 1:1 basis, stratified by site, to receive either the ‘Better Conversations with Primary Progressive Aphasia’ intervention (21 couples) or no speech and language therapy treatment (21 couples). Participants are recruited by SLTs who will conduct pre-intervention assessment (week 1) and deliver the intervention (weeks 2 to 5). Junior researchers, who are blinded to allocation, will complete post-intervention measures (week 6). SLTs complete 9 h of training to prepare them to deliver the intervention. The primary objective of the study is to establish for a phase III effectiveness study whether the program can be delivered as intended in a UK National Health Service setting. Specifically, it will establish (1) the acceptability of randomisation, (2) an assessment of treatment fidelity to determine necessary levels of SLT training, (3) the most appropriate primary outcome measure, (4) sample size requirements, (5) predicted patient recruitment and retention rates and (6) refined inclusion criteria.

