### Pre- and post-intervention measures

Participants will complete pre-intervention language, communication and quality of life measures (see Table 2) with the local collaborator in week 1 of the study. Completing assessment to gain an insight into areas of communication strength and difficulty prior to commencing intervention is routine procedure in speech and language therapy practice, and importantly, provides the opportunity for local collaborators to build rapport with participants before delivery of the intervention. All measures will be repeated after intervention at week 6 by a pair of junior researchers. In order to collect communication data, participants will be trained to independently use an iPad to video record conversation samples. A conversation topic list will be provided to support this process should they require it. Table 3 summarises the schedule of pre- and post-intervention measures.

**Table 2 Tab2:** List of pre- and post-intervention measures

Language measures: 1. Comprehensive Aphasia Test [43] This language battery provides a profile of performance across all modalities of language production and comprehension.	
Communication measure: 1. Video recordings of conversation samples This informal measure adapted from the Aphasia Conversation Measure [21] identifies barriers and facilitators to conversation between the person with PPA and their CP and assesses changes in conversation after intervention	
Quality of life measures: 1. Dementia Quality of Life Measure [44] This questionnaire is designed to ask people with dementia to rate their quality of life across the three main domains of feelings, memory and everyday life. 2. The Aphasia Impact Questionnaire [45] A tool designed to measure the impact of living with aphasia across three domains of communication, participation and emotional well-being. 3. Communication Confidence Rating Scale for Aphasia [42] This is a questionnaire of communication confidence that uses a self-rating scale designed for people with aphasia. 4. Perceived Stress Scale [46] (completed by CP only) This is a self-report questionnaire for measuring the respondent’s perception of stress. 5. Zarit burden interview [47] (completed by CP only) This is a caregiver self-report questionnaire for measuring personal and care strain.

**Table 3 Tab3:** Schedule of pre- and post-intervention measures

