### Criteria for success

This study will be considered appropriate to proceed to a full trial if:▸Patients and local collaborators report generally positive views about acceptability of randomisation and of intervention as determined by evaluation of feedback forms;▸A suitable sensitive outcome measure is determined and sample size estimated;▸Local collaborator intervention-fidelity rate is at least 80%.

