Study limitations include the inability to blind participants to group allocation, a common barrier in behavioural studies. Those allocated to the control group will not receive any intervention for 4 weeks as there is no comparable standard care intervention. Similarly, it is not possible to blind local collaborators delivering the intervention. For this reason, post-intervention assessment is not completed by the local collaborators but by pairs of junior researchers who will be blinded to group allocation. The inclusion criteria for this study may result in significant heterogeneity across participants in terms of language profile and communication difficulties, making it difficult to compare participants’ skills pre and post intervention. Thus, a range of outcome measures are being piloted across language, communication, and quality of life to identify the most sensitive across all participants. BCPPA is designed to be tailored to an individual’s needs, which may result in variation in the types of strategies identified and practiced. To counter this, the key components of BCPPA remain fixed, and measures of fidelity will demonstrate the consistency with which the intervention in delivered. A further potential limitation is ascertainment bias since access to speech and language therapy for PPA varies widely across the UK, and some of the likely barriers to access (socio-economic, cultural, linguistic, etc.) could also influence BCPPA outcomes. Despite these limitations, this study represents an important step toward a future full-scale RCT to determine the effectiveness of BCPPA for people with PPA and their family members.

The results of this study will be disseminated via presentations at national and international conferences and submitted for publication in peer reviewed scientific journals. In the medium term, the BCPPA program and training materials will be made available to SLTs via UCL’s public e-learning platform, alongside BCA [18]. With support from the study steering committee, results will be disseminated through professional and user group networks via publications and presentations, for example, at the PPA support group branch of the Rare Dementias Support Group based at UCL (http://www.raredementiasupport.org/).

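### The same pilot ANOVA results are to choose the full trial's outcome and feed its power calculation; if the chosen measure's observed effect is used, the full trial is likely to be undersized

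*Protocol article*

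**What the plan says.** Under Data analysis, the protocol article enters the language and quality-of-life data into a repeated measures ANOVA with group as the between-subject factor and time (before and after therapy) as the within-subject factor. The next statement is: "This information will be used to determine a suitable sensitive outcome measure and to perform a power calculation". The conversation counts are described after that and have their own test.

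The Discussion gives the purpose of having several measures: "a range of outcome measures are being piloted across language, communication, and quality of life to identify the most sensitive across all participants". Under Criteria for success, the second condition for going on to a full trial is: "A suitable sensitive outcome measure is determined and sample size estimated".

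Table 2 lists one language measure, one communication measure and five quality-of-life measures. The ANOVA sentence therefore covers six, and the Discussion's wording covers seven. On the pilot's own size, Sample size justification says: "As there are no data available to estimate a sample size, the recruitment of participants has been dealt with pragmatically". The article gives no minimum important difference for any measure, does not define sensitive, and does not say which ANOVA quantity enters the power calculation.

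**The concern.** In a two-group, pre/post ANOVA, a measure's sensitivity to treatment shows in the interaction, that is, in the observed difference between arms in change. Choosing a measure because this difference is large, and then planning from the same difference, is selection followed by estimation on the same data. The winner's estimate contains its own favourable chance error, so it is biased upward. Sample size varies with the inverse square of the effect, so a moderate bias becomes a large shortfall.

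The primary outcome and the sample size are two of the six things the pilot is meant to establish (Aim). The harm would fall on the later trial, which could be launched with too little power to find a real benefit.

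**Working it through.** **Inputs from the article.** 42 couples randomised 1:1, so 21 per arm (Abstract; Sample size justification). Six ANOVA measures, or 1 + 1 + 5 = 7 in Table 2. The 42 is a recruitment estimate with no effect size, SD or power behind it, so there is no power-based figure to reproduce.

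**Assumptions, because the article gives none.** Two-sided 5% test, 80% power, no dropout, change scores scaled to SD 1, a common correlation ρ between measures, selection of the largest observed standardised effect d, and that d used to plan the full trial.

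**Precision of the pilot.** SE(d) ≈ √(2/21) = 0.309, so the 95% half-width is about 1.96 × 0.309 ≈ 0.6. At 21 per arm, power is 37% for a true d of 0.5 and 74% for 0.8.

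**Size of the selection bias, by hand.** The largest of six independent standard normal values averages about 1.27. With no true effect and ρ = 0, the best of six should average 1.27 × 0.309 = 0.39; simulation gives 0.40. With ρ = 0.3 the factor is √(1 − 0.3) = 0.84, giving 0.33; simulation gives 0.34.

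**One case in full: best of six, ρ = 0.3, true d = 0.5.**
- Median selected d is about 0.85.
- Planned n per arm = 2(1.96 + 0.8416)²/0.85² = 21.7, so 22, plus 1 for the t-test = 23.
- Needed n per arm = 2(2.8016)²/0.5² = 62.8, so 63 (64 with the t-test correction).
- True power at 23 per arm is about 38%: the noncentrality is 0.5 × √(23/2) = 1.70, against a critical value near 2.

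**Simulation, equal true effects (4,000 pilots per row).** N is the total for the full trial.

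| Measures | True d | ρ | Mean selected d | Median planned N | N needed | Median true power |
|---|---|---|---|---|---|---|
| 6 | 0.3 | 0 | 0.71 | 66 | 350 | 23% |
| 6 | 0.3 | 0.3 | 0.64 | 78 | 350 | 26% |
| 6 | 0.3 | 0.5 | 0.60 | 92 | 350 | 30% |
| 6 | 0.5 | 0 | 0.92 | 40 | 126 | 35% |
| 6 | 0.5 | 0.3 | 0.86 | 44 | 126 | 38% |
| 6 | 0.5 | 0.5 | 0.81 | 50 | 126 | 42% |
| 7 | 0.3 | 0 to 0.5 | 0.74 to 0.62 | 60 to 84 | 350 | 21% to 28% |
| 7 | 0.5 | 0 to 0.5 | 0.96 to 0.82 | 36 to 48 | 126 | 32% to 41% |

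Mean power is higher than the median but still low: 27% to 48% over the six-measure rows.

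**How much is selection and how much is noise.** With a single pre-stated measure and true d = 0.5, the mean observed d is 0.51, so there is essentially no bias. Planning from that noisy estimate still gives a mean power of only 72%. Selecting the best of six at ρ = 0.3 lowers the mean to 44%.

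**One dominant measure (true d 0.8, the others 0.2), ρ = 0 to 0.5.** The right measure is chosen in about 72% to 89% of pilots, and true power is about 56% to 72%. With seven measures the mean selected d is 0.89 to 0.83.

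**The case against.** The strongest reply is that the article never says the winner's observed effect becomes the target difference. The same ANOVA data yield an SD and a pre-post correlation, which are proper things to carry forward, and a condensed article may leave the source of the target difference to the full protocol. This stands as a limit on certainty, so the shortfall is conditional. It does not remove the point. The article does state that one set of results serves both purposes, and it names no other source for the effect.

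A reader might infer more than the text supports in four ways.
- *That the rule is to take whichever measure moved most.* Data analysis and Criteria for success ask for a suitable and sensitive measure. Only the Discussion speaks of the most sensitive, and no largest-effect rule is written.
- *That the second success criterion can never fail.* This holds only if sensitive means having the largest observed effect. If it means a detectable change, the criterion can fail: with seven measures, ρ = 0.3 and no true effects, about 72% of pilots show no p below 0.05. The criterion is undefined, but it has not been shown to be empty.
- *That seven measures feed the quoted step.* Read in place, the sentence covers six. The bias is nearly the same.
- *That the full trial will certainly be badly undersized, around the wrong outcome.* Equal-effect simulations cannot show a wrong choice, since no measure in them is better than another. The Discussion itself suggests the measures may differ: communication confidence might improve without a clear change in language measures. Where one measure dominates, the choice is usually right and the loss of power is smaller.

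It is also fair that responsiveness is a legitimate property to weigh when choosing an outcome, and that nothing in the pilot's own conduct or feasibility results is affected.

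**Conclusion.** The concern holds in conditional form. The article ties outcome selection and the power calculation to the same small data set, with no external target difference and no guard against selection. If the selected measure's observed effect is used, it is likely to be inflated and the full trial undersized. A nominal 80% would typically be about 22% to 42% when the measures share a true effect of 0.3 to 0.5 with correlation 0 to 0.5, and about 56% to 72% when one measure truly dominates (0.8 against 0.2). The true effects, correlations, test level, power and absence of dropout are assumptions, not figures from the article. If only the SD and correlation are carried forward alongside a separately justified difference, this bias does not arise, but the article does not say so. Severity: should-fix.

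**What to change.** 1. In Data analysis, state that the pilot supplies the SD, pre-post correlation and retention for the sample size. State also that the target difference will be a pre-stated important difference, justified by outside evidence or by judgement with clinicians and couples, and not the selected measure's pilot effect.
2. State the criteria for choosing the outcome in advance: completeness, floor and ceiling effects, relevance to couples, and whether it can be assessed blind. Report pilot responsiveness with confidence intervals, as supporting information only.
3. Reword the second item under Criteria for success so that it refers to those criteria and to a sample size built on the pre-stated difference. Align the Discussion sentence on the most sensitive measure.

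No extra participants, visits or data are needed. The costs are that the projected full-trial sample size will probably be larger, and that a target difference must be argued for where the article says no data exist. Adding a margin for uncertainty in the pilot SD, such as an upper confidence limit, is a reasonable option but a matter of preference.

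### The conversation counts are tested before versus after with no between-arm contrast, and the Poisson test gives p-values that are too small if the counts are overdispersed

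*Protocol article*

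**What the plan says.** The Data analysis section describes two separate analyses.

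- **Language and quality-of-life scores.** "Repeated measures ANOVA will be used in the analysis with group (no speech and language therapy treatment, BCPPA treatment) as a between subject factor", with time as the within-subject factor. The group-by-time term gives a randomised comparison.
- **Conversation data.** The procedure is carried over from the BCA programme. Its purpose is "to identify change in the use of targeted strategies following intervention", and it works by "counting barrier and facilitator behaviours in 5-min video samples selected from the pre- and post-intervention conversation samples". Then: "These counts will be analysed using Poisson Trend Test suitable for observations occurring in Poisson distribution". On the contrast: "All pre-therapy conversations will be weighted the same as one another, as will all the post therapy conversations". On differences between couples: "Outcomes for different participants will be investigated using a Test for Homogeneity, where this is significant", after which dyad-level effects are obtained with Holm-Bonferroni.

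The design is a parallel-group comparison with a no-therapy control. According to the Abstract, "Participants will be randomised on a 1:1 basis, stratified by site", with 21 couples per arm. Table 2 lists the conversation recordings as the only communication measure. Table 3 schedules four recordings before treatment (two with an assessor on site, two made independently at home) and four after (one with an assessor, three at home).

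**The concern.** Every step described for the counts is either before-versus-after or dyad-by-dyad. Arm appears in none of them. The control group is therefore unused for the measure closest to what the intervention aims to change. Disease progression, growing familiarity with being filmed, and the change in recording mix shown in Table 3 all fall into the same contrast as BCPPA.

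The test also takes its variance from the Poisson model. The clips are repeated observations on the same couple in different settings. If counts vary between conversations of one couple by more than Poisson, or if couples change by different amounts, the standard error is too small.

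The results have a use beyond this pilot. The Aim section lists choosing the main-trial primary outcome and calculating its sample size, and Criteria for success makes both a condition for proceeding. A before-after Poisson result supplies neither a between-arm effect nor a between-dyad variance for that calculation. It would also set the conversation measure beside ANOVA-tested measures on an unequal footing.

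**Working it through.** The protocol gives no count rate, dispersion, significance level or power for this test, and its sample size is pragmatic, so there is no planned figure to reproduce. The checks below use stated assumptions.

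**Inputs from the protocol:** 21 couples per arm; four recordings before and four after.
**Assumptions:** two-sided 5% level; all eight recordings used, one clip each; mean 10 behaviours per clip unless stated.

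**1. Change common to both arms, no BCPPA effect, pure Poisson counts.** The expected total before is 21 × 4 × 10 = 840. With a common time ratio r the expected total after is 840r, and the test statistic is centred at (840r − 840)/√(840r + 840).

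- r = 1.05: 42/√1722 = 1.01, so rejection is about Φ(1.01 − 1.96) = 17%.
- r = 1.10: 84/√1764 = 2.00, so rejection is about Φ(2.00 − 1.96) = 52%.

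Simulation (5,000 runs, couples differing in level with a coefficient of variation of 0.5) agrees:

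| Common ratio | 21 dyads | 42 dyads pooled |
|---|---|---|
| 0.85 | 0.89 | 0.99 |
| 0.90 | 0.55 | 0.84 |
| 1.00 | 0.05 | 0.05 |
| 1.05 | 0.17 | 0.30 |
| 1.10 | 0.51 | 0.81 |
| 1.15 | 0.84 | 0.99 |

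The protocol does not say whether the test is run within each arm or on all couples. Running it in each arm and comparing the two p-values does not help. At r = 1.10, the chance that BCPPA alone is significant is 0.51 × 0.49 = 0.25, with no treatment effect.

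**2. A shift from the recording mix alone.** Suppose home clips carry 1.2 times the rate of assessor clips (an assumption). The mean relative rate before is (2 × 1 + 2 × 1.2)/4 = 1.10, and after it is (1 × 1 + 3 × 1.2)/4 = 1.15. The ratio is 1.15/1.10 = 1.045, close to the 1.05 row, with nothing else changing.

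**3. Overdispersion, no change of any kind.** If the variance is φ times the mean, the true size of the nominal 5% test is 2 × [1 − Φ(1.96/√φ)].

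| φ | 1.96/√φ | True size | Homogeneity test rejects | At least one dyad significant at first Holm step |
|---|---|---|---|---|
| 1 | 1.96 | 5% | about 5% | 4–5% |
| 1.5 | 1.60 | 11% | 39–40% | 21–24% |
| 2 | 1.39 | 17% | 71–73% | 42–48% |
| 3 | 1.13 | 26% | 95–96% | 77–82% |

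The last two columns are simulated with 21 dyads, no true differences, and means of 5, 10 and 20 per clip. The Holm column applies if the dyad step is run. A further simulation, with mean 8 per clip and φ = 1, let couples' log change vary with SD 0.2 around zero. The pooled test then rejected in about 15% of runs.

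**4. The same data with an arm comparison.** A t-test between arms of each couple's log(post/pre) ratio, 21 versus 21 with no BCPPA effect, rejected in 4.3% to 5.3% of runs across φ of 1, 2 and 3 and common ratios from 0.85 to 1.15.

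**The case against.** **The excess false-positive rate from overdispersion is assumed, not shown.** This stands. A reader might infer that the p-values are certainly too small, but the protocol gives no dispersion figure, and at φ = 1 the size is correct. Stable differences in level between couples cancel in a before-after contrast, so the heterogeneity conceded in the Discussion does not settle it. Extra-Poisson variation across topics and settings is plausible, and the Discussion expects tailoring, "which may result in variation in the types of strategies identified and practiced". The statement must nevertheless stay conditional.

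**The plan includes a homogeneity test.** It does, and where dispersion is large the pooled result would often be flagged. The 11% to 26% figures are thus the size of the pooled test, not of the whole sequence. But the homogeneity test uses the same Poisson variance, so it takes overdispersion for real differences between couples and passes the problem to the dyad-level tests. In the scenario with SD 0.2, couples do truly change, so those rejections are wrong only as statements about the average.

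**The outcome might seem undefined for controls**, because targeted strategies are set in therapy. The documents do not support that inference. The next sentence of Data analysis counts barriers and facilitators, and Table 2 applies the measure to the whole trial. These behaviours can be counted in any couple, so the phrase needs tidying only.

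**This is a pilot, reported in a condensed article.** Efficacy is not its primary aim, the sentence on selecting an outcome follows the ANOVA text, and nothing makes the Poisson p-value the selection rule. That lowers the severity. It does not remove the point, because the article names the test, the weights and the follow-up tests, so this is a stated analysis and not a detail left out. The Discussion also counts communication among the domains being compared for sensitivity.

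**Conclusion.** The point holds, with moderate severity. The missing between-arm contrast is plain from the text and rests on no assumption. As written, the analysis cannot separate BCPPA from anything else that changes between the two sets of recordings. How much this matters depends on the common change: under the assumed mean of 10 per clip and all eight recordings, a 5% shift gives about 17% (21 dyads) or 30% (42 dyads) spurious rejections, and a 10% shift gives 51% or 81%. The Poisson variance is a second, conditional weakness: about 11%, 17% or 26% true size at variance ratios of 1.5, 2 or 3, and no inflation at 1. It would go too far to conclude that the pilot's decision to proceed depends on this test. What is at risk is the evidence for selecting the conversation measure and sizing a trial on it.

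**What to change.** Make the between-arm difference in change the main analysis of the conversation counts. Either of these would do:

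- an arm-by-period rate ratio with 95% CI from a quasi-Poisson or negative binomial model clustered on dyad; or
- a simple comparison between arms of each couple's log(post/pre) ratio, which is easier to support with 42 couples and held its size in the check above.

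In either case account for site, the stratification factor, and for recording setting, because its mix changes between periods. State that the same barrier and facilitator behaviours are counted in both arms. Keep the dyad-level Poisson and Holm-Bonferroni results as descriptive. Report the between-dyad variance of change, which the main-trial sample size needs.

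The cost is a change of analysis wording and minor extra analysis work, with no new data. Intervals will be wider than those of the Poisson before-after test, because they carry the between-couple variation and the comparison with controls.
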